### Randomization, allocation concealment, and blinding

Patients meeting the inclusion criteria will be randomly assigned to the intervention group and control group at a 1:1 allocation ratio after recruitment. The randomly assigned list will be computer-generated (using the website: http://randomization.com) and executed by a statistician who is not clinically involved in this study. The randomization list will be kept in a sealed, opaque envelope by the project manager who is in charge of the capsule distribution, and inaccessible to anyone else. Therefore, except for the project manager, the investigators, the data collectors, and the patients are blind to the patient’s allocation treatment and the composition of each capsule supplement. Other researchers will know the patient’s allocation and each capsule supplement composition only after the completion of this study. If needed, the investigators will be informed which supplements each patient received. After the trial is completed, participants in the control group will have the opportunity to participate in a 30-day LBP supplement program.

### Measurement

The data collector will record the patients’ demographic data, diagnostic methods, and clinical diagnosis and the participant’s anthropometric examination, laboratory assessment, and imaging. Other information regarding insulin resistance, gut microbiota and intestinal permeability, physical-activity, patient compliance, and adverse events will be noted by the researcher.

### Clinical evaluation

Clinical evaluation including patient’s characteristic demographic data (sex, age, nationality, address, telephone number) and anthropometric examination such as height, weight, fat-free weight, BMI, body fat, body fat ratio, waist-hip ratio, and other indicators. The anthropometric examination will be measured with a body composition analyzer (InBody, InBody770). InBody770 is a body composition analyzer of direct segmental multi-frequency bioelectrical impedance analysis (DSM-BIA) method, which is fast, non-invasive, and accurate. The patient demographic data will be carefully assessed and recorded by the investigator before the intervention. The anthropometric results will be evaluated at the beginning of the intervention and at the last follow-up visit.

### Laboratory assessment and imaging

Laboratory investigations include liver enzymes (γ-glutamyltransferase (GGT), alanine aminotransferase (ALT), and aspartate aminotransferase (AST)); biochemical markers of lipogenesis such as triglycerides (TG), total cholesterol (TC), LDL-cholesterol, HDL-cholesterol, and free fatty acids (FFA); and inflammatory factors (IL-6, IL-1β, TNF-α, MCP-1). At baseline and 12 weeks, the blood sample will be collected for laboratory evaluation after a 12-h overnight fasting. Liver enzymes and lipid profiles (TG, TC, LDL-cholesterol, HDL-cholesterol) will be measured by an automatic biochemistry analyzer. The levels of FFA will be assayed using an FFA assay kit (Nanjing Jiancheng Bioengineering Institute, Nanjing, China). Gas chromatography-mass spectrometer (7890B-5977A GC/MSD, Agilent, USA) will be used for the short chain fatty acids (acetic acid, propanoic acid, butyric acid, isobutyric acid, N-valeric acid, isobutyric acid, caproic acid) analysis. The concentration of inflammatory factors will be determined by enzyme-linked immunosorbent assays (ELISA) kit (Elabscience Biotechnology Institute, China). All laboratory assessments will be performed in the same laboratory by using standard laboratory methods. At the beginning and the end of the intervention period, ultrasound examination of the abdomen will be performed on all patients, and the hepatic steatosis will be noted and graded.

### Insulin resistance

The homeostasis model assessment for insulin resistance (HOMA-IR) index will be used to determine the degree of insulin resistance of individuals. It will be calculated by using the formula: [fasting plasma insulin (mU/L) × fasting plasma glucose (mmol/L)]/22.5. All individuals will be advised to fast overnight before blood sample collection. The blood sample collected in the EDTA anticoagulant tubes will be centrifuged and plasma stored at -80 °C for a series of tests. Fasting plasma insulin will be detected by using an ELISA kit (Elabscience Biotechnology Institute, China). Fasting plasma glucose will be instantly measured by the One Touch Ultra 2 blood glucose meter (LifeScan, USA). The testing of insulin and glucose will be performed on each patient at weeks 0 and 12 follow-up assessments.

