### Study participants

All patients with NAFLD treated at the physical examination center of the Ningxia Hui Autonomous Region People’s Hospital will be recruited and invited to participate. The specific inclusion criteria are (1) subjects diagnosed with NAFLD through the abnormal liver enzymes and ultrasonography, (2) aged 45~59 years, and (3) willing to participate in the study and sign informed consent. Patients will be excluded if they have (1) acute or chronic viral hepatitis, drug-induced liver disease, liver cirrhosis, or other causes of chronic liver disease; (2) alcohol consumption > 140 g/week in men or > 70 g/week in women over the past 6 months; (3) intestinal diseases or other chronic inflammation; and (4) diabetes or uncontrolled cardiovascular disease. Other exclusion criteria include regular intake of probiotic supplements or food within 3 months, pregnancy, and use of medications such as corticosteroid drugs, immunosuppressants, and antibiotics.

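### Fasting glucose for HOMA-IR is read on a blood glucose meter although fasting blood already goes to a laboratory analyser at the same weeks: a small, avoidable loss of precision

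*Protocol article*

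**What the plan says.** The Insulin resistance section of the protocol article defines HOMA-IR by the formula "fasting plasma insulin (mU/L) × fasting plasma glucose (mmol/L)]/22.5". Both terms are labelled plasma. Insulin is assayed by ELISA. For glucose the section says: "Fasting plasma glucose will be instantly measured by the One Touch Ultra 2 blood glucose meter (LifeScan, USA"). On timing it says: "The testing of insulin and glucose will be performed on each patient at weeks 0 and 12 follow-up assessments". It also has EDTA blood centrifuged and the plasma frozen for later tests.

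The section Laboratory assessment and imaging says: "At baseline and 12 weeks, the blood sample will be collected for laboratory evaluation after a 12-h overnight fasting". It continues: "Liver enzymes and lipid profiles (TG, TC, LDL-cholesterol, HDL-cholesterol) will be measured by an automatic biochemistry analyzer". It then adds: "All laboratory assessments will be performed in the same laboratory by using standard laboratory methods". Neither glucose nor insulin is among the analytes listed there.

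Under Study participants, the exclusions include "diabetes or uncontrolled cardiovascular disease".

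The article describes no laboratory glucose measurement, no duplicate meter readings and no check of the meter against the analyser.

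**The concern.** The trial has fasting blood and a biochemistry analyser available at both time points where glucose is needed, yet it takes glucose from a different and presumably less precise device. Because diabetes is excluded, fasting glucose probably spans a narrow range and any effect of the supplement on it is likely to be small. Device error then makes up a larger share of the spread between patients than it would in a diabetic population. HOMA-IR is a product, so a proportional error in glucose passes straight into the index at each of the two time points. At stake is some precision for fasting glucose and a little for HOMA-IR, in a trial sized on ALT alone.

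**Working it through.** The article gives no SD, assay precision or power for glucose or HOMA-IR, so there is no stated figure to reproduce. Two illustrations follow. Their inputs are assumptions, except the 25 patients per arm from Sample size calculation.

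**1. Variance of a single glucose reading**

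Assumed: mean fasting glucose 5.5 mmol/L, between-patient SD 0.5 mmol/L, and an error-free reading as comparator.

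Error SD = CV × 5.5. Rise in variance = (error SD / 0.5)².

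| Meter CV | Error SD (mmol/L) | Rise in variance |
|---|---|---|
| 3% | 0.165 | 0.109, about 11% |
| 5% | 0.275 | 0.303, about 30% |
| 7.5% | 0.413 | 0.681, about 68% |
| 10% | 0.55 | 1.21, about 121% |

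**2. Change from week 0 to week 12, meter against analyser**

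Assumed, on the log scale: analyser CV 2%; meter CV 3% to 10%; insulin assay CV 8%; SD of biological change 0.06 to 0.10 for glucose and 0.25 to 0.45 for insulin; changes in glucose and insulin independent.

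- Variance of glucose change = (biological SD)² + 2 × CV². The factor 2 is for the two readings.
- Variance of HOMA-IR change = variance of insulin change + variance of glucose change, since the log of a product is a sum.
- The multiplier on the sample size needed is the variance with the meter divided by the variance with the analyser.

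Middle setting (biological SDs 0.08 and 0.35, meter CV 5%):

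- Glucose, analyser: 0.0064 + 2 × 0.0004 = 0.0072
- Glucose, meter: 0.0064 + 2 × 0.0025 = 0.0114
- Glucose multiplier: 0.0114 / 0.0072 = 1.58
- Insulin: 0.1225 + 2 × 0.0064 = 0.1353
- HOMA-IR multiplier: (0.1353 + 0.0114) / (0.1353 + 0.0072) = 0.1467 / 0.1425 = 1.03

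Extremes of the grid:

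- Best case (SDs 0.10 and 0.45, meter CV 3%): glucose 0.0118 / 0.0108 = 1.09; HOMA-IR 0.2271 / 0.2261 = 1.004
- Worst case (SDs 0.06 and 0.25, meter CV 10%): glucose 0.0236 / 0.0044 = 5.36; HOMA-IR 0.0989 / 0.0797 = 1.24

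To express this as power, set the effect so that the analyser would give 80% with 25 per arm at two-sided 5%. With the meter, power at the middle setting is 61% for glucose and 79% for HOMA-IR. In the best case it is 76% and 80%; in the worst, 23% and 71%.

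The cost falls mainly on glucose taken alone. HOMA-IR is little affected because variation in insulin dominates it. A positive correlation between the glucose and insulin changes would add the same covariance to numerator and denominator and bring the HOMA-IR multiplier closer to 1.

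**The case against.** The best defence is that the article states one method openly, uses it in both arms at both time points, and that a better assay is only a preference. Much of this stands, and it rules out several stronger readings.

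- **Contradiction.** A reader might infer that the meter conflicts with the sentence on one laboratory and standard methods. That sentence closes the article's own list under Laboratory assessment and imaging, which does not include glucose. The Measurement section also names insulin resistance under other information, apart from laboratory assessment. A conflict is not clearly shown.
- **Damage to a declared outcome.** Neither glucose nor HOMA-IR is named in the abstract's outcomes or under Outcome measures. They could enter the secondary list only through its general reference to laboratory results. Their outcome status is ambiguous at most.
- **Wrong specimen.** A reader might take the meter to be reading capillary whole blood mislabelled as plasma. The article does not say which specimen is applied to the meter or what quantity it reports, so this cannot be settled from the text.
- **Bias.** Both blinded arms use the same device on the same schedule. Random error costs precision, and a constant offset would shift absolute values in both arms alike.
- **An uninterpretable null result for HOMA-IR.** This does not fit a multiplier of about 1.03 at the middle setting.

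The defence can also say that an immediate reading may be deliberate, because glucose in a drawn sample depends on how it is handled. That is a fair condition on the remedy. It does not explain why an analyser in use at the same weeks is passed over.

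**Conclusion.** The point holds as a minor, inexpensive improvement. The meter adds random error that the trial could avoid with blood it already draws. The documents support the direction; the size rests on assumptions. With a mean of 5.5 mmol/L, an SD of 0.5 and an error-free comparator, single-reading glucose variance rises by about 11% to 121% for a meter CV of 3% to 10%. Those figures somewhat overstate the gain from switching, since an analyser has error too. For HOMA-IR, the only use of glucose that the article states, the sample-size multiplier is about 1.00 to 1.24. The treatment comparison is not biased, and the ALT outcome and the planned 50 participants do not depend on this point.

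**What to change.** In the Insulin resistance section, state that fasting glucose at weeks 0 and 12 is measured on the laboratory's automatic biochemistry analyser from the fasting blood already drawn, with prompt separation of the sample, and that this value enters HOMA-IR. Use the same method at both time points for each patient. This matters because Trial status reports recruitment under way, and a change of device between weeks 0 and 12 would mix any difference between devices into that patient's change.

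The cost is one added analyte at two time points and prompt sample handling. No extra visit or procedure is needed.

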### Gut microbiota and intestinal permeability

The stool (take two samples every time) will be collected at the baseline before the intervention and the end of 12 weeks intervention for the gut microbiota analysis. The participants will be instructed to collect, store, and transport the fecal samples on proper methods. A convenient specimen collection box will be provided to all patients before the beginning of the intervention. They will be advised to take 2–3 g of fecal samples each time and then immediately store the samples into their own freezer (at least -20 °C). Afterwards, the individuals will notify the researchers to transfer the samples to a -80 °C refrigerator until analysis. For the gut microbiota assessment, total DNA will be extracted from 150 mg of fecal with the QIAamp DNA mini kit (Qiagen, Valencia, CA, USA). The purity and concentration of DNA will be detected by gel electrophoresis for sequencing and bioinformatics analysis. Raw reads will be filtered to remove adaptors and low-quality and ambiguous bases, and then paired-end reads will be added to tags by Fast Length Adjustment of Short reads program (FLASH, vl.2.11) to get the tags. The tags will be clustered into OTUs with a cutoff value of 97% using UPARSE software (v7.0.1090) and chimera sequences will be compared with the Gold database using UCHIME (v4.2.40) to detect. The sequencing data will be analyzed by QIIAME v1.8.0. In addition, the short chain fatty acid (SCFA) concentrations will be determined in the fecal supernatant using the gas chromatograph-mass spectrometer (Agilent 7890B-5977A, USA) for sample analyzing and using ChemStation software (Agilent, USA) for data handling.

The intestinal barrier function and permeability will be determined by the concentration of serum claudin-3 and LPS in plasma. As described above, the blood samples will be used to evaluate the changes of claudin-3 and LPS concentration before and after the intervention. According to the manufacturer’s instructions, serum biomarkers claudin-3 will be measured by ELISA, and the LPS will be performed through the limulus test method.

### Physical-activity

Physical activity will be assessed by using the International Physical Activity Questionnaire-Short Form (IPAQ) [22] at 0, 4, 8, and 12 weeks. They are instructed not to change the current level of physical activity throughout the study. The participants will be provided with a smart activity tracker (Xiaomi, China), which could monitor blood oxygen saturation, heart rate, blood pressure, exercise steps, calories, and sleep situation. Participants will be instructed to wear monitors at least 5 days a week and the data on the monitor worn by the participants will be recorded at each follow-up. It will be used to assess how much time participants spend on physical exercise each week.

## Outcome measures

### Primary outcome measure

The primary outcome measure will be a significant ALT concentration relief after the intervention, which is assessed and recorded by the researchers according to the results of laboratory assessment.

### Secondary outcome measures

The following is the secondary outcome:
Gut microbiota abundance and diversity assessed by metagenomic sequencing method.Intestinal permeability determined by the concentration of claudin-3 and LPS.Patient’s characteristic demographic data by investigating and the results of laboratory assessment and the body composition evaluated by anthropometry.Patient’s compliance and adverse effects.

### Sample size calculation

Based on the previous study results of supplementing synbiotics in NAFLD, this study took the significant reduction of ALT concentration as the main outcome indicator for sample size calculation. According to the research of Eslamparas et al. [23], it was found that the concentration of ALT decreased 11.3 and 4.4 in the intervention and control groups respectively. It aimed to determine an appropriate target sample size that would provide a 90% power (*β* = 0.10) for two-tailed testing with 5% type-1 error rate of the measure. Using the PASS 22.0 software, we calculated a minimum requirement of 42 patients for total. In practice, we decided to enroll a total of 50 participants (*n* = 25 per group), taking into account the 20% drop-out rate before the end of the study.

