### Study design

This is a single-center, two-group (1:1), prospective, randomized, double-blind, placebo-control study. The present protocol was designed in accordance with the Standard Protocol Items: Recommendations for Interventional Trials (SPIRIT) guidelines and completed the SPIRIT Checklist [21] (Additional file 1). Additionally, the whole study design is illustrated in Fig. 1 and a SPIRIT figure is presented in Fig. 2.

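### Enrolling 50 does not cover the stated 20% drop-out: it leaves 40 completers against a stated minimum of 42, a small arithmetic error worth at most about 1.5 points of power

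*Protocol article*

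**What the plan says.** All the relevant figures are in the protocol article under Sample size calculation. The assumed effect comes from an earlier synbiotic study in NAFLD, in which "the concentration of ALT decreased 11.3 and 4.4 in the intervention and control groups respectively". The calculation is meant to "provide a 90% power" "for two-tailed testing with 5% type-1 error rate of the measure". From this the authors report that "we calculated a minimum requirement of 42 patients for total". They then fix enrolment at 50, 25 per group, "taking into account the 20% drop-out rate before the end of the study". The 1:1 allocation is confirmed under Study design.

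Two other sections bear on the point. Laboratory assessment and imaging schedules the blood sample, and so ALT, at baseline and week 12 only. Data analysis says that all randomized patients are to be analysed, with multiple imputation for missing data.

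**The concern.** A drop-out allowance is meant to ensure that the number left after the expected losses is at least the calculated minimum. Here the minimum, the drop-out rate and the enrolment are all printed, and the enrolment is too small for the other two. If the plan's own drop-out assumption comes true, the trial finishes below the number that the plan calls its minimum. Enrolment, drop-out rate and power therefore cannot all stand as written. What is at stake is the accuracy of the power statement for the primary outcome, ALT.

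**Working it through.** **Inputs from the protocol article**
- Minimum for 90% power: 42 in total, 21 per group (Sample size calculation).
- Enrolment: 50 in total, 25 per group (Sample size calculation).
- Drop-out: 20% (Sample size calculation).
- Difference in ALT decrease: 11.3 − 4.4 = 6.9 (Sample size calculation).
- Two-sided 5% test (Sample size calculation); 1:1 allocation (Study design).

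**Reproducing the 50**
- Multiplying up: 42 × (1 + 0.20) = 50.4, which rounds to 50. This is the likely route to the stated figure.
- Allowing for loss: 42 / (1 − 0.20) = 52.5, so 53. By arm, 21 / 0.80 = 26.25, so 27 per arm and 54 in total.

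**Completers at the stated enrolment**
- 50 × (1 − 0.20) = 40, that is 20 per group and 2 below the minimum.
- Largest loss that still leaves 42: 50 − 42 = 8, and 8 / 50 = 16%.

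**Size of the power loss**

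The section prints no standard deviation, so I assume that 42 is correct and solve backwards. For n per arm, the t-test has 2n − 2 degrees of freedom and noncentrality 6.9 / (SD × √(2/n)).

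- 21 per arm gives exactly 90% at SD = 6.73, a standardised difference of 6.9 / 6.73 = 1.025.
- 20 per arm gives exactly 90% at SD = 6.56. So 21 per arm is the minimum for SDs above 6.56 and up to 6.73.

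| Completers per arm | Power at SD 6.73 (t-test) |
|---|---|
| 20 | 88.5% |
| 21 | 90.0% |
| 25 | 94.4% |

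Over the SD range 6.56 to 6.73, power at 20 per arm runs from just under 90% down to 88.5%. A normal approximation puts the SD range at 6.73 to 6.90 and the lowest power at 20 per arm at 88.6%. The choice of formula therefore does not change the conclusion.

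**The case against.** **The effect is negligible and conditional.** The 90% is attached to 42 patients, and 50 enrolled keeps 42 through 8 losses. The shortfall appears only with 9 or more losses. At the full 20% it is at most about 1.5 points, and with no losses the power is about 94%. All of this stands, and it limits the point to a small correction. It does not remove the inconsistency between the printed figures.

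**Multiple imputation keeps all 50 in the analysis.** This does not clearly restore the power. ALT is taken only at baseline and week 12, so a participant lost before week 12 has no post-baseline value. Imputing from baseline adds little information about the treatment effect. The authors also inflated the sample for drop-out, so their own calculation treats those patients as lost.

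**A reader might infer that the trial is seriously underpowered because the true SD could be much larger than 6.7.** The article gives no basis for a larger SD, and with one 42 would no longer be the minimum. Most of any resulting fall in power would come from the SD chosen, not from the drop-out slip.

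**A reader might also treat the unprinted SD and unit as a defect in their own right.** A condensed article may leave such inputs to the full protocol, which is not shown. They are not counted here. Their absence only means that the power at 40 completers has to be given as a range.

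**Conclusion.** The inconsistency is certain and needs no outside figure: 50 with 20% drop-out leaves 40, below the stated minimum of 42. It is a minor arithmetic error. The power at 40 completers lies between about 88.5% and just under 90%, on the assumptions that 42 is the correct minimum, that the difference is 6.9 and that the test is an equal-variance two-sample t-test at two-sided 5%. The article does not name the procedure used in the software, and unequal SDs would imply other values. The statement that 50 enrolled tolerates up to 16% drop-out needs none of these power assumptions. The documents do not support a claim that the design fails to reach 90% power in general, since it falls short only if more than 8 of the 50 are lost.

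**What to change.** Keep enrolment at 50 and correct the sentence in Sample size calculation in one of two ways:

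1. State that 50 enrolled allows for a drop-out of up to 16%, leaving 42 completers and 90% power. This follows directly from the plan's own numbers and is the safer wording.
2. Keep the 20% and state that 40 completers then give slightly under 90% power (about 88.5% at the lowest), with the figure computed by the authors from the SD used in their calculation.

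Either change costs one sentence and no extra patients. The downside is a slightly less favourable drop-out allowance or power figure. If the authors want to keep both 20% drop-out and 90% power, the consistent enrolment is 53, or 54 at 1:1, which is 3 or 4 more participants. For an error of this size that is optional.
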